#### GTR

Until today there are no studies analyzing the GTR in rnTMS compared to sham, but only studies with nTMS. Picht et al. [25] demonstrated a GTR of 61% in the intervention group versus 45% in the control group (OR 1.91). We expect a higher difference in our groups due to the induction of plasticity in this intervention. We expect an OR of 2.85 or higher (for example for proportions of 74% vs. 50% of GTR in the intervention vs. control group). Using information of 66 sham and 66 rnTMS patients it will be possible to demonstrate such a difference using a chi-square test (power=82%, two-sided significance level of 0.05) (nQuery Advisor 8). The statistical analysis will be done using binary logistic regression accounting for the center and age group. Using this analysis strategy will result in at least the same or higher power.

Both primary hypotheses will be tested hierarchically at a two-sided significance level of 0.05. To account for possible dropouts (approximately 10%), 148 patients in total will be included in the study to ensure at least 132 complete cases, even if we apply missing value imputation methods using 30 complete data sets (if missing at random (MAR) or missing completely at random (MCAR) assumption holds). To evaluate if individual missings are MAR, MCAR, or missing not at random (MNAR) we will use information on reasons of missings or dropouts (e.g. if patients drop out due to worsening of health status or not). In case of premature death (before measuring the primary outcome, the BMRC score for those patients will be set to the worst possible value.

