### Trial design {8}

The trial is designed as a randomized, triple-blind, sham-controlled, bicentric parallel-group two-arm non-inferiority trial. Patients will be allocated 1:1 to the two groups. Patients, outcome assessors, and the trial statistician will be blinded to the group allocation. An overview of the trial timeline can be found in Fig. 1.

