### Participant timeline {13}

The study is planned to run from March 2023 until July 2025, with recruitment starting in October 2023 in both recruitment centers. Participants are recruited from the regular incoming patients via advertisements, ambulatory care, or the in-patient ward. They will undergo MRI imaging, a clinical assessment, and nTMS assessment as part of the clinical routine. Following these screening procedures, eligible patients will be invited to participate in the study and randomized. The rnTMS intervention will be applied for 5–28 days twice daily, depending on the individually available presurgical time. Each rnTMS session is followed by a short motor training. Ideally on the day following the last rnTMS session, depending on the surgical schedule, patients will undergo resection of the tumor. Follow-up measurements are scheduled immediately after the rnTMS intervention (T1), 7 days postoperatively (T2), and 3 months postoperatively (T3). Table 1 gives an overview of study visits and timepoints as well as the procedures performed per timepoint.

**Table 1 Tab1:** Participant timeline

**Study procedure**	**Screening**	**Baseline**	**Intervention**	**After intervention**	**Surgery**	**7 days post-operative**	**3 months post-operative**
Visit number		T0		T1		T2	T3
Study day	−1	0	0–5/28	5/28	6/29	13/36	3 months
Informed consent	X						
Inclusion/exclusion criteria	X						
Demographics, medical/neurol. history	X						
nTMS measurement	X			X			
Motor status (BMRC)^a^		X		X		X	X^a^
Structural MRI incl. assessment of GTR^a^	X			X		X^a^	
EORTC-BN20		X		X		X	X
ARAT		X		X		X	X
Diffusion-weighted MRI	X						
Resting-state fMRI	X			X			
rnTMS stimulation			X				
Motor training			X				
(Serious) adverse events^b^		X	X	X	X	X	X
Details of surgery					X		
Tumor histology						X	

Depending on the individually available time before surgery, patients enrolled in the study can have varying treatment durations (5–28 days) and thus, complete their study visits on different study days. The first follow-up measurement (T1) is always performed immediately after the intervention and before surgery. The surgery is then performed on the day after the last treatment, that is, the earliest on study day 6 or the latest on study day 29. Postoperative follow-ups are performed 7 days (T2) and 3 months (T3) after surgery, i.e. the earliest on study day 13 and the latest on study day 36 for T2 and respectively 3 months later for T3

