#### Description of the primary efficacy analysis and population

(1) Non-inferiority of motor status at T3 in the rnTMS group vs. sham group will be tested using an ordinal regression model (adjusted for baseline motor status) with dependent variable motor status at T3 (ordinal: six categories). Additionally, center, duration of rnTMS/sham training, and age will be included as covariates. Non-inferiority is successfully proven, if the upper limit of the 95% CI of the odds ratio for a worse outcome in the intervention group is below 1.35 according to the pre-specified non-inferiority margin. (2) The second main hypothesis, that the GTR is higher in the rnTMS compared to the sham group, will be tested (only if the first hypothesis has been proven, hierarchical testing) at a two-sided significance level of *α* = 0.05 using a binary logistic regression model with gross total resection (yes/no) as a dependent variable, group allocation, center, duration of rnTMS/sham training, and age as independent variables. A per-protocol analysis will be conducted as a sensitivity analysis.

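### The 82% power for gross total resection is that of a stand-alone test; because it is tested only after non-inferiority is shown, the chance of claiming it is at most 80%, and about 66% if the two tests are independent

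*Protocol article*

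**What the plan says.** In the Protocol article, the GTR part of Sample size {14} assumes an odds ratio of 2.85 or more, "for example for proportions of 74% vs. 50% of GTR in the intervention vs. control group". It continues: "Using information of 66 sham and 66 rnTMS patients it will be possible to demonstrate such a difference using a chi-square test", with "power=82%, two-sided significance level of 0.05". The paragraph that follows says the two primary hypotheses are tested hierarchically.

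The order is fixed under Description of the primary efficacy analysis and population. Non-inferiority of motor status at 3 months comes first, and GTR superiority is tested "only if the first hypothesis has been proven, hierarchical testing". The Motor status part of Sample size {14} gives the first test 80% power at one-sided 0.025. The Efficacy paragraph of Statistical methods {20a} then attaches one power figure, 80%, to the hierarchical test of both hypotheses.

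Section {18b}, on retention and follow-up, expects no missing values for GTR, because early postoperative imaging is part of routine care. The article gives neither a joint power nor a correlation between the two endpoints.

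**The concern.** In a fixed sequence the second hypothesis can be claimed only when the first has also been shown. Its power in the planned procedure is the probability that both tests succeed, and this cannot exceed the power of the first test. The 82% makes no allowance for the sequence. It is above the 80% stated for the test that must be passed first, so it cannot be the chance that the trial demonstrates higher GTR.

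Higher GTR is one of the two primary hypotheses and the only one framed as superiority. Someone judging the trial's prospects, or later reading a GTR result that was not significant or was never formally tested, would take from the article a chance of success of about four in five. The design delivers that only in the limiting case where every trial that shows non-inferiority also shows GTR superiority.

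**Working it through.** **Inputs**
- GTR rates 74% and 50%, 66 per arm, chi-square test, two-sided 0.05 (Sample size {14}, GTR).
- Equal allocation: "Patients will be allocated 1:1 to the two groups" (Trial design {8}).
- Power of the first test 80%, taken as stated (Sample size {14}, Motor status).
- GTR tested only after success on the first test (Description of the primary efficacy analysis and population).
- 148 patients randomised, that is 148 / 2 = 74 per arm, with no missing GTR expected (Sample size {14}; {18b}).

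**Step 1: reproduce the 82%.** Power = Φ[(p1 − p2 − 1.96 × SE0) / SE1], where SE0 uses the pooled rate (0.74 + 0.50)/2 = 0.62.
- SE0 = √(2 × 0.62 × 0.38 / 66) = 0.0845
- SE1 = √(0.74 × 0.26 / 66 + 0.50 × 0.50 / 66) = 0.0819
- (0.24 − 1.96 × 0.0845) / 0.0819 = 0.909, and Φ(0.909) = 81.8%

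Exact enumeration of the same test gives 82.3%. The stated 82% is right for a test that is always carried out.

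**Step 2: apply the sequence.** Let A be success on non-inferiority, with P(A) = 0.80, and B be success on GTR, with P(B) = 0.82.
- Independent tests: 0.80 × 0.82 = 0.656, or 66%.
- Lower bound under any dependence: 0.80 + 0.82 − 1 = 0.62.
- Upper bound under any dependence: min(0.80, 0.82) = 0.80.

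With bivariate normal test statistics the joint probability is:

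| Correlation | Both succeed |
|---|---|
| −0.5 | 62.7% |
| 0 | 65.6% |
| 0.3 | 68.1% |
| 0.5 | 70.1% |
| 0.8 | 74.1% |

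**Step 3: all randomised patients contribute to GTR.** With 74 per arm:
- SE0 = √(2 × 0.62 × 0.38 / 74) = 0.0798 and SE1 = √(0.74 × 0.26 / 74 + 0.50 × 0.50 / 74) = 0.0773
- (0.24 − 1.96 × 0.0798) / 0.0773 = 1.08, giving stand-alone power of 86%
- Independent tests: 0.80 × 0.86 = 0.688, or 69%
- Bounds: 0.80 + 0.86 − 1 = 0.66, and 0.80

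The larger GTR sample raises the joint figure by about three percentage points under independence. The 80% ceiling stays.

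**Step 4: what the 82% is not.** The probability of GTR success given success on the first test is P(A and B) / P(A). From the stated figures it lies between 0.62 / 0.80 = 77.5% and 0.80 / 0.80 = 100%. It equals 82% only under independence, so 82% is the marginal power and not a conditional one.

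**The case against.** The best defence is that nothing has been miscalculated. The 82% is tied to a named test with a named sample size, it reproduces, and the next paragraph says that testing is hierarchical. Quoting power hypothesis by hypothesis in a fixed sequence is common, and the Discussion calls the trial exploratory. All of this stands, and it makes the point one of labelling rather than arithmetic. It does not rescue the Efficacy paragraph, where one 80% is attached to testing both hypotheses. The article's remark that logistic regression would have at least the power of the chi-square test does not help either, because the ceiling comes from the first test.

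A reader might infer four stronger things that the document does not support.

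- *That the plan's own figures give 66%.* They give 62% to 80%. The 66% needs independence, which the article neither states nor justifies. Both endpoints come from the same patients, and the correlation could have either sign.
- *That 66 per arm is the only relevant GTR sample.* Section {18b} expects complete GTR data, so up to 74 per arm may contribute.
- *That the assumed 50% control rate is too low.* The article cites a study that "demonstrated a GTR of 61% in the intervention group versus 45% in the control group (OR 1.91", and says of its own patients: "They will undergo MRI imaging, a clinical assessment, and nTMS assessment as part of the clinical routine". One could reason that the sham arm should resemble the cited study's 61% arm. But the article does not say what that study's controls received, it offers 74% against 50% only as an example, and its eligibility rules select tumours in or close to motor pathways.
- *That the GTR figure should be far lower because the motor-status power is itself overstated.* That is a separate question about the non-inferiority calculation. It is not settled here, and the figures above take the stated 80% at face value.

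**Conclusion.** The point holds as one of labelling, with a definite size. The 82% is correct as stand-alone power but is not the power to claim GTR superiority under the planned sequence. That power cannot exceed 80%. It is 66% if the tests are independent and 62% to 80% under any dependence, or 69% (66% to 80%) if all 74 per arm contribute GTR data. The 80% in the Efficacy paragraph is supported for the first hypothesis only, since for the second it is the upper limit.

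These figures rest on the stated 80% for non-inferiority and on the assumed rates of 74% and 50%. If the first power were revised downward, the ceiling on the second would fall with it. The error rate, the tests and the order of testing are not affected.

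**What to change.** - In Sample size {14}, GTR, label 82% as the stand-alone power of the chi-square test, before the testing order is taken into account. Do not call it conditional power.
- Add the power for GTR under the sequence: about 66% with independent tests, range 62% to 80%, naming the correlation assumption. If complete GTR data are expected, add the figures for 74 per arm: 86% stand-alone, 69% under independence, range 66% to 80%.
- In the Efficacy paragraph of Statistical methods {20a}, restrict the 80% to the first hypothesis.
- Note that the GTR figure falls further if the non-inferiority power is revised downward.

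The cost is a few sentences and a less favourable stated power. Sample size, tests and testing order stay as they are.

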### Recruitment {15}

A recent clinical trial [10] applying postoperative rnTMS treatment screened 430 patients with gliomas in the vicinity of motor-relevant areas over a time period of 4 years for study eligibility. In this comparable patient group, 12% of patients did not agree to participate in the study. This would resemble roughly 150 patients willing to participate in the study for each study center across the recruitment period of 19 months, of which 74 have to be recruited.

As part of the study, three different patient workshops will be conducted to involve patients in the study from the beginning. This may have a positive impact on recruitment as patients can give valuable insights on suitable methods and timepoints for study advertisement, while considering the potentially overwhelming preoperative period.

Furthermore, participation in the study will not delay surgery or impact the neurosurgical treatment. We also aim to ease participation in the study by organizing and compensating for travel to the study site if needed.

## Assignment of interventions: allocation

### Sequence generation {16a}

Patients will be randomly allocated (1:1) to the trial arms stratified by recruitment center (Berlin, Heidelberg) and age (< 55 years, ≥ 55 years). The randomization list will be produced by the study biostatistician using a block randomization with varying block sizes.

### Concealment mechanism {16b}

Patients will receive their randomization via the inbuilt tool in the Research Electronic Data Capture (REDCap) software. Different access groups will be defined in the REDCap software, so that only interventional staff has access to the randomization list of patients. Conversely, interventional staff will not have access to document outcomes in the software. These assessments can only be accessed by outcome assessors.

### Implementation {16c}

The randomization list will be used as input for the randomization tool inbuilt in the REDCap software by the trial statistician and recruited patients will be allocated to their respective treatment arms via this software.

Patients are enrolled by a blinded study physician; outcomes are assessed by blinded staff. Only the intervention staff performing the rnTMS intervention are not blinded to the treatment allocation and have access to the randomization list.

## Assignment of interventions: blinding

### Who will be blinded {17a}

The study is designed as a triple-blinded study. Patients, assessors of the outcomes, and the biostatistician are blinded to group allocation of patients. Only the interventional staff performing the rnTMS intervention are not blinded to the treatment allocation and have access to the randomization list. The performing neurosurgeon is informed about the trial participation of the patient but blinded towards the group allocation.

### Procedure for unblinding if needed {17b}

Premature unblinding of a study patient can be considered for medical reasons and in case of severe adverse events. Attending physicians and investigators are encouraged to discuss these requests with the principal investigator. The reason, time, and date of the unblinding will be documented on case report forms (CRF) and study monitors will be informed.

## Data collection and management

### Plans for assessment and collection of outcomes {18a}

The documentation of the surgery as well as the TMS and MRI examination is done via regular patient records. The collection, documentation, and management of experimental data (study data) is done in a study file. Among other things, data on age and gender as well as data on comorbidities and medical history are collected (see {13,19}).

Study data will be collected exclusively in pseudonymous form via digital recording and test forms (eCRFs). These data will be collected and stored via the REDCap platform. Data entry is controlled by access groups ensuring blinding of all personnel. Anatomical/tractography and connectivity data are further stored pseudonymously on a local hospital data server. Electromyographic and navigation data from the TMS examination will be collected via the TMS device and then also stored on the local hospital data server. The name, day, and month of birth of each patient will not be stored in the REDCap database but linked to patient data records by a unique identifier. Corresponding personal data will be maintained in paper format by each participating center. All paper data will be maintained in a locked room and locked cabinet.

### Plans to promote participant retention and complete follow-up {18b}

Regarding the primary outcome measure BMRC score at 3 months follow up we expect a low rate of missings of around 2% [25, 26]. However, to ensure a sufficient number of complete cases the rate of loss to follow up a more conservative 10% rate of dropout is assumed. For the second primary outcome GTR, we expect no missing values since early postoperative structural MRIs are measured as part of the clinical routine and available to all patients.

Postoperative follow-ups are scheduled before release from the ward (T2) or coinciding with regular medical follow-up visits (T3). To promote participant retention, travel to the hospital can be organized by the investigators and financially compensated (for example costs for a taxi). See also {11c}.

### Data management {19}

Study data will be gathered on electronic case report forms, stored in the data management software REDCap, and secured with back-ups of the data dictionary on an external hard drive together with the raw data from TMS and MRI measurements.

Data collection is controlled by an external monitor according to standard operating procedures. The Clinical Trial Office (CTO) at Charité will monitor the correct completion and perform plausibility checks of the data stored in REDCap to avoid discrepancies with the source data. Implausible or missing data will be queried. The data from both study centers will be entered directly in a central REDCap database provided by the coordinating center. Access groups will be defined to assure blinding. REDCap further provides an audit trail for all activities. The coordinating center will provide a training to all users of REDCap during this study.

The database will be locked after completion of data collection and final data review. All relevant study data will be archived by the coordinating investigator for 10 years according to local regulations.

### Confidentiality {27}

The data collected within this study will be used exclusively for the purpose of managing and conducting the study and for the purpose of research and evaluation.

The documentation of all study patients (study data) is done separately from the medical record via a study file. Data collection, data storage, and data analysis will be performed exclusively after pseudonymization. The coding list, which allows the study-related data to be linked to the identifying information of the participants, can only be accessed by the study management and individual persons authorized by it. The coding list will be maintained in paper form. It will be kept in a lockable cabinet and destroyed after ten years. All other documents kept on paper, such as consent forms, etc., will also be kept in a lockable cabinet at the respective study site. Digitally captured pseudonymous study data is stored on the REDCap platform. The study database is also backed up regularly to a local hospital data server. Data collected electronically during the study (anatomical data/tractography and connectivity data/electromyography (EMG) and navigation data from the TMS examination) are also stored pseudonymously on this server. Access to the data collected during the study is regulated within the study team by the principal investigator. The coordinating investigator at the second study center [name]. [name] as well as the members of the study team of the Department of Neurosurgery at Heidelberg University Hospital will be provided with study data for the purpose of evaluation, whereby data transmission will always be in pseudonymized and encrypted form. In the same context, pseudonymized study data of the Heidelberg Center will be made available to the principal investigator [name]. [name], and the staff of the Department of Neurosurgery of the Charité.

The study participants are informed that the study physicians may inspect the patient file for the purpose of evaluation and release the treating physician from the medical confidentiality obligation in this case.

The participants have the possibility to explicitly agree to the transfer of the pseudonymized data to research institutions and clinics within the European Union.

### Plans for collection, laboratory evaluation, and storage of biological specimens for genetic or molecular analysis in this trial/future use {33}

Not applicable, no samples were collected.

## Statistical methods

### Statistical methods for primary and secondary outcomes {20a}

#### Efficacy

To test both main hypotheses of comparable motor status at T3 and a higher GTR in rnTMS patients compared to sham patients, we will apply hierarchical testing at a two-sided significance level of *α* = 0.05 (Power = 80%). Primary hypotheses will be tested in an intention-to-treat (ITT) framework using multiple imputed datasets in case of missing values (under the assumption of MCAR or MAR) after a single imputation of informative missing values (MNAR) for example for patients with worsened health status or patients who die during follow up.

#### Description of the primary efficacy analysis and population

(1) Non-inferiority of motor status at T3 in the rnTMS group vs. sham group will be tested using an ordinal regression model (adjusted for baseline motor status) with dependent variable motor status at T3 (ordinal: six categories). Additionally, center, duration of rnTMS/sham training, and age will be included as covariates. Non-inferiority is successfully proven, if the upper limit of the 95% CI of the odds ratio for a worse outcome in the intervention group is below 1.35 according to the pre-specified non-inferiority margin. (2) The second main hypothesis, that the GTR is higher in the rnTMS compared to the sham group, will be tested (only if the first hypothesis has been proven, hierarchical testing) at a two-sided significance level of *α* = 0.05 using a binary logistic regression model with gross total resection (yes/no) as a dependent variable, group allocation, center, duration of rnTMS/sham training, and age as independent variables. A per-protocol analysis will be conducted as a sensitivity analysis.

